### Secondary endpoint measures

Secondary endpoints are: hospital mortality rate, ICU admission rate, cardiac arrest call rate, length of stay and usability as measured by the System Usability Scale (SUS) score. An increased ICU admission rate could be interpreted a marker of improved practice or worse practice. We hypothesise that earlier ICU admission will results in a shorter length of stay, lower ICU mortality and lower APACHE II acute physiology score on admission to ICU. These data will also be included in the secondary endpoints to aid interpretation of ICU admission rates.

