**Methods:**

This study is a non-randomised stepped wedge evaluation carried out across the four hospitals of the Oxford University Hospitals NHS Trust, comparing charting on paper and charting using SEND. We assume that more frequent monitoring of acutely ill patients is associated with better recognition of patient deterioration.

The primary outcome measure is the time between a patient’s first observations set with an Early Warning Score above the alerting threshold and their subsequent set of observations. Secondary outcome measures are in-hospital mortality, cardiac arrest and Intensive Care admission rates, hospital length of stay and system usability measured using the System Usability Scale. We will also measure Intensive Care length of stay, Intensive Care mortality, Acute Physiology and Chronic Health Evaluation (APACHE) II acute physiology score on admission, to examine whether the introduction of SEND has any effect on Intensive Care-related outcomes.

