### Statistics

#### Analysis of outcome measures

A time to event analysis will be carried out to compare the primary outcome measure for paper-based charting with SEND-based charting. Competing events, such as transfer to theatre or cardiac arrest, may prevent a second set of observations being taken. Common electronically-recorded competing events are listed in Table 1. The time and type of any of these events will be recorded if they occur within 14 h of the triggering set of observations. If another set of observations or a competing event is not found within 14 h from the first triggering observation set it will be assumed that no further observations took place.

The time point of the step and ward will be included as covariates. The study design is multi-level, patients within ward, and a multi-level model will be used to take into account the correlation between patients within ward. Other covariates at the patient and ward level will be included in the models. A detailed statistical analysis plan will be written prior to analysis, however it is expected that the method for the primary outcome will be in the form of a semi-parametric random effects model, such as those described by Scheike et al. [31] and Zhou et al. [32].

Secondary endpoints will be reported for each period ward combination. A patient may be admitted to ICU more than once, but only the first ICU admission will be considered for the analysis. For each period-ward combination the probability of admission to ICU will be calculated from the number of patients admitted to ICU at least once and the total number of patients.

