## Discussion

Measuring the effect of implementing a novel clinical information system is challenging. The practicalities of rolling out a system safely and effectively rarely permit a randomised study. The before-and-after design, which has been used frequently in the past, is subject to bias from confounding variables. We hope this study will provide a model for others to follow in the future.

The stepped-wedge design is well suited to the study of a phased roll-out. If properly analysed, adjusting for time and other confounding variables, the quality of evidence from a stepped wedge trial approaches that of a randomised controlled trial [34]. The best methods of modelling the data remain a subject for debate [35]. We will explore different approaches as part of our analysis.

The best metric to use for the primary endpoint is also challenging. Previous studies have used mortality and length of stay. We find it implausible that the introduction of a new charting system could significantly affect these endpoints alone. Length of stay, in particular, is affected by many external factors. Therefore we report these as secondary endpoints.

The incidence of admission to ICU is a measure related to patient deterioration but its interpretation is unclear. A rise in referrals may either indicate an increased awareness of patient deterioration or it may indicate an increased incidence of deterioration. It is also confounded by the fact that behavioural and systemic factors may inhibit admission to ICU, even if deterioration is recognised.

Our chosen metric, the time from the first triggering observation set to the subsequent observation set, has the benefit of being easy to measure on both paper and electronic charting systems. In contrast to ICU referral, the factors influencing the timing of the second set of observations are largely within the control of the attending nurse.

We have not chosen to measure the response to every triggering observation set as we anticipate that nursing behaviour will change to repeated alerts from an individual patient. Repeated alerting may indicate failure to adequately to treat deterioration but it may also reflect that some treatments take many hours to have an effect. In the latter situation gradually decreasing the frequency of observations may be appropriate.

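### ICU stay, ICU mortality and admission APACHE II score describe a group that SEND may change, so lower values alone cannot be read as earlier admission or benefit

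*Protocol article*

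**What the plan says.** Under Secondary endpoint measures the article concedes the ambiguity: "An increased ICU admission rate could be interpreted a marker of improved practice or worse practice". It then hypothesises that earlier ICU admission leads to a shorter stay, "lower ICU mortality and lower APACHE II acute physiology score on admission to ICU". It gives these measures a task: "These data will also be included in the secondary endpoints to aid interpretation of ICU admission rates". The abstract makes clear that Intensive Care length of stay is among them and states the aim more broadly, as "to examine whether the introduction of SEND has any effect on Intensive Care-related outcomes".

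Under Analysis of outcome measures, "only the first ICU admission will be considered for the analysis", and the probability of ICU admission is "calculated from the number of patients admitted to ICU at least once and the total number of patients". No denominator is stated for ICU mortality. Secondary endpoints are to be reported for each combination of period and ward.

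The Discussion returns to the admission rate: "A rise in referrals may either indicate an increased awareness of patient deterioration or it may indicate an increased incidence of deterioration". It adds that behaviour and the wider system can hold back ICU admission even after deterioration has been recognised. Neither section extends this caution to the three ICU-only measures.

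**The concern.** ICU admission happens after SEND is switched on and is itself an endpoint that SEND might move. A comparison of stay, mortality or severity among ICU patients under paper and under SEND therefore compares two groups that the intervention may have selected differently. The named time-varying covariates (nurse staffing and the SHMI case-mix adjustment) do not describe selection into ICU.

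The favourable pattern named in the article is lower on all three measures. A lower threshold that brings in milder patients gives the same pattern. At stake is the reading of a rise in ICU admissions: measures added to clarify it could make a change in who is admitted look like earlier rescue of the same patients.

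**Working it through.** The article has no figure of its own to reproduce here. Its only power calculation concerns the primary outcome, and it gives no ICU admission rate, mortality, stay or score. Every input below is an assumption.

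**Formula.** Let m0 be the mean in patients who would have gone to ICU anyway, me the mean in the added patients, and x the number added per original ICU patient. The observed mean is (m0 + x·me)/(1 + x). The change from m0 is x(me − m0)/(1 + x), which is negative whenever me < m0.

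**Main illustration.** Without SEND, 2% of ward admissions go to ICU, with 20% mortality, a mean stay of 5 days and a mean score of 12. SEND adds milder patients (5%, 2 days, score 8) and changes nothing for the original ones. For 0.5 percentage points added:

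- ICU mortality: (0.02 × 0.20 + 0.005 × 0.05)/0.025 = 0.00425/0.025 = 17.0%
- ICU stay: (0.02 × 5 + 0.005 × 2)/0.025 = 0.110/0.025 = 4.4 days
- Score: (0.02 × 12 + 0.005 × 8)/0.025 = 0.28/0.025 = 11.2

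| Added (percentage points) | ICU mortality | ICU stay (days) | Score |
|---|---|---|---|
| 0 | 20.0% | 5.0 | 12.0 |
| 0.25 | 18.3% | 4.7 | 11.6 |
| 0.5 | 17.0% | 4.4 | 11.2 |
| 1.0 | 15.0% | 4.0 | 10.7 |

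**Sensitivity.** With m0 = 25%, score 15, stay 5 days, 20% more admissions and the same added patients, mortality becomes (0.25 + 0.20 × 0.05)/1.20 = 21.7%, score (15 + 0.20 × 8)/1.20 = 13.8 and stay (5 + 0.20 × 2)/1.20 = 4.5 days. Over m0 of 15% to 35%, me of 2% to 10% and x of 5% to 30%, ICU mortality always falls. The smallest fall is about 0.2 points (15% to 14.8%) and the largest 7.6 points (35% to 27.4%).

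**What would discriminate.** Per 1,000 ward admissions, let H ICU admissions lie above a fixed score and L below it, with H + L = 20 (2% of 1,000).

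- Threshold shift adding 5 milder patients, all below the cut: H unchanged, L + 5.
- Earlier admission of the same patients, moving k of them across the cut: H − k, L + k, total still 20.
- Higher incidence with unchanged mix and the same total rise (25/20 = 1.25): 1.25H and 1.25L.

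Both of the first two lower the mean score among ICU patients. Only earlier admission lowers H.

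**The case against.** Four points can be made for the plan.

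1. *There is no decision rule.* A reader might infer that the article commits itself to reporting lower values as proof of benefit. It does not: it states a one-way hypothesis and calls the data an aid. It also says elsewhere that SEND contains nothing aimed at the response of doctors and the organisation, so its authors do not seem set to claim an ICU benefit. This stands, and it limits the point to how the measures may be read.

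2. *The measures are not empty.* A reader might infer that they cannot separate any of the explanations. Delayed recognition should raise the admission score, and higher incidence alone gives no clear reason for it to fall, so the score does carry information against those two. This stands too. The explanation that it cannot exclude is a lower threshold.

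3. *Safeguards are planned.* Hospital mortality and the ICU admission probability cover all patients. Multiplying that probability by ICU mortality recovers ICU deaths per ward patient (0.025 × 0.17 = 0.00425). These are partial guards, but neither shows whether the original ICU patients arrived earlier.

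4. *ICU deaths or bed-days per ward admission would be poor replacements.* In the main illustration deaths rise from 4.0 to 4.25 and days from 100 to 110 per 1,000 ward admissions, and a reader might infer that this exposes harm. It does not. Suppose, again by assumption, that the 5 added patients per 1,000 would have had 10% mortality on the ward and have 5% in ICU. Then 5 × (0.10 − 0.05) = 0.25 lives per 1,000 are saved, yet ICU deaths still rise to 4.25, because deaths have moved from ward to ICU. This stands in full.

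The article also defers detail to an analysis plan that is not shown. That excuses missing modelling detail, but the interpretive role and the expected direction are stated in the article itself.

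**Conclusion.** The point holds as a limit on interpretation. ICU stay and admission score are necessarily confined to ICU patients, and ICU mortality is so in its ordinary meaning, which is an inference because no denominator is given. Since SEND may alter that group, a fall in all three is compatible with earlier admission and equally with a lower threshold. Such a fall is uninterpretable on its own rather than false: truly earlier admission would also lower the score.

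The size is unknown from the documents. Under the assumptions used, a rise from 2.0% to 2.5% in ICU admissions takes ICU mortality from 20% to 17.0% with no original patient affected. The direction rests only on the added patients being milder than the existing ones. The supporting secondary endpoints are affected; the primary outcome and the sample size are not.

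**What to change.** - Add ICU admissions with an acute physiology score above a cut fixed before analysis, per 1,000 eligible ward admissions, and likewise those below it. Estimate the SEND effect with the same ward and period adjustment as for the primary outcome.
- Label ICU stay, ICU mortality and mean score among ICU patients as descriptive, and state that lower values do not by themselves show earlier admission.
- Interpret them beside all-patient hospital mortality and the ICU admission rate. This matters for the new rates too, since severe ICU admissions could also fall for reasons other than earlier admission.
- If ICU deaths or bed-days per ward admission are reported, present them as measures of location or resource use, not of benefit or harm.

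The cost is wording in the protocol and analysis plan plus one further analysis. The ICU data (ICNARC) and the total patient count are already planned. The downsides are that a severity cut must be chosen in advance, that the rates are small and so imprecise, and that earlier admission which does not carry a patient across the cut will not be seen.

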### Data collection procedures

SEND will be rolled out in the four hospitals sequentially. Data collection will occur in a single hospital at any one time. At each site, collection of data from SEND will occur on all wards where SEND is being used for the duration of roll out. During a single admission episode patients will only contribute primary endpoint data from the first study ward to which they are admitted.

Collection of data from paper charts will occur on all wards where paper charts are being used. The time of first eligible triggering observations set and the time of the subsequent observations set will be collected by retrospective inspection of charts by a single assessor. Where no subsequent observations set exists the reason, where it can be inferred, will be noted (Table 1).

**Table 1 Tab1:** Competing events which affect observation recording times

Competing Events
Cardiac arrest
Death
Discharge or transfer to another hospital
Medical emergency but not cardiac arrest
Palliation
Transfer to another ward
Transfer to ICU
Transfer to surgery

ICU-related data will be collected from the Intensive Care National Audit and Research Centre (ICNARC) database, length of stay and hospital mortality will be collected from the hospital Patient Administration System (PAS), cardiac arrest data will be collected from the Trust’s cardiac arrest audit database.

Time-varying covariates will be collected and included in the statistical model. These will include nurse staffing levels and the Standardised Hospital Mortality Ratio (SHMI) case-mix adjustment. In common with other software, the SEND application will be updated periodically to address issues raised by users and improve features. The release dates of new software versions will be recorded and may be included in the analysis. Other unanticipated events or changes in hospital process which are likely to impact on the performance of the SEND system will be documented if observed.

User feedback will be collected using a questionnaire consisting of the SUS questions supplemented by additional questions regarding the respondents’ demographics and experiences using the system [Additional file 2]. The SUS score is a validated measure of system usability [29].

Following completion of roll-out at a site all users at the site will be invited to complete the questionnaire. The questionnaire will be administered electronically. The questionnaire has been formatted following best practices [30]. Users will be given the opportunity to opt-out of receiving further emails. Except for those who have opted out, users who do not complete the questionnaires will be sent two reminders via email.

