### Aim

The aim of this study is to determine whether introduction of SEND affects nursing recognition and response to signs of patient clinical deterioration.

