### Hypothesis

The OUH NHS Trust has implemented the Centile-based Early Warning Score (CEWS) which defines at-risk patients as having a CEWS score of 3 or more [26]. Trust protocols mandate that a repeat observation of the vital signs should be performed within 1 h whenever a patient is at risk. Local audit suggests that these standards are not consistently met. Similar problems have been observed in other institutions [8, 22].

It is anticipated that SEND may affect the adherence to local policies on the frequency of observation recording for patients. As a result the observation frequency may change. A number of system features have the potential to contribute to this change. Integration of a tablet with vital signs monitors has previously been shown to reduce the time taken to record observations [27]. Preliminary data suggest that charting using SEND is faster than on paper. Lowering staff workload may improve observation frequency. SEND provides on-screen prompts and auditing of performance. Such measures have been shown to improve the frequency of observation recording [22]. However, staff are used to paper-based systems, which are readily accessible. Poor implementation of electronic vital signs systems has previously resulted in decreased charting rates [28].

Frequent patient observation is necessary but not sufficient to affect clinical outcome measures. The translation of improved management of deteriorating patients by nursing staff to better patient outcomes is dependent on the response of doctors as well as organisational facilities and processes – the “effector arm”. The implementation of SEND does not contain any measures designed to specifically improve the effector arm, therefore use of measures such as mortality or length of stay as the primary endpoint would not be suitable for assessing whether SEND improves nursing management. Nevertheless, these are clinically important measures and will be reported as secondary endpoints.

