### Inclusion and exclusion criteria

The study period will commence two weeks prior to the roll out of SEND on the first ward in the initial hospital and finish three months after the roll out of SEND on the final ward in the final hospital. During this period all patients over the age of 16 years admitted to a study ward will be included, unless Trust protocol dictates that their observations should be recorded on a maternity observation chart. Admission episodes in which vital signs are charted on both paper and electronic systems during a single admission will also be excluded.

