### Sample size

The number of patients included in the study will primarily be pragmatic. All eligible admissions will be included for the first hospitals. A subsequent interim analysis will determine what proportion of eligible admissions within a study ward in the paper charting cohort will be included for the final hospital, the largest of the four institutions. If the analysis determines that fewer than 100 % of admissions are required then admissions will be randomly selected. All eligible admissions where data is recorded using SEND will be included for all four hospitals. We anticipate that the total number of admissions included in the study will be around 60,000.

Power calculation for the first hospital is based upon analysis of (currently unpublished) data from a previous trial conducted locally. We assume that the proportion of patients who have a further observation within three hours of a recording an EWS ≥3 will be 0.5 in the paper arm (as seen in a previous study) and 0.6 in the electronic arm, that there will be an average of 11 patients with an initial EWS ≥3 per cell, and conservatively that the intra-cluster correlation (ICC) will be 0.15, the power is estimated to be 79.3 % for a 5 % alpha level.

This calculation depends on statistics estimated from the one small study. However it does indicate that when including all four hospitals the study will be sufficiently powerful to detect a difference of 10 % in the primary outcome between groups.

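### The comparison is defined by the chart used, and every mixed-chart admission is dropped, so patients whose staff partly reverted to paper after activation leave the estimate of SEND's effect

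*Protocol article*

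**What the plan says.** The Aim section states the question as "to determine whether introduction of SEND affects nursing recognition and response to signs of patient clinical deterioration". The Methods section describes a one-way stepped wedge: SEND goes live for all patients on a ward together, is not withdrawn, and practice is assessed before and after each step.

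The sentences that define the cohorts use the chart medium:

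- Analysis of outcome measures: the analysis is to "compare the primary outcome measure for paper-based charting with SEND-based charting".
- Sample size: "All eligible admissions where data is recorded using SEND will be included for all four hospitals".
- Data collection procedures: "collection of data from SEND will occur on all wards where SEND is being used for the duration of roll out", and "Collection of data from paper charts will occur on all wards where paper charts are being used".
- Inclusion and exclusion criteria: "Admission episodes in which vital signs are charted on both paper and electronic systems during a single admission will also be excluded".

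No section ties a patient's exposure to the activation date of the ward, and none says what happens to observations written on paper on a ward that has already been activated.

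**The concern.** If the question is what introducing SEND does to re-observation, every eligible triggering set on an activated ward is part of the answer, including those where staff went back to paper for some of the stay. The mixed-charting exclusion removes the partly reverted episodes. It acts on something that happens after exposure begins, possibly after the triggering set, and that belongs to the recording process the primary outcome measures.

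The exclusion has a sensible use for transfers between paper and SEND wards and for stays that span the switch. As worded, it also reaches a patient admitted after activation whose ward used paper for part of the stay.

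Some reversion is foreseeable. The Hypothesis section notes that staff are accustomed to paper and can easily reach it, and that "Poor implementation of electronic vital signs systems has previously resulted in decreased charting rates". The SEND Implementation Plan places project staff on each ward for two weeks to find problems. If fallback happens under system failure or workload pressure, the excluded episodes could be those with the slowest re-observation, and the estimate would then overstate the benefit of introduction.

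**Working it through.** **Inputs from the Protocol article (Sample size).** Proportion re-observed within 3 h: 0.5 on paper, 0.6 with SEND. The planned effect is 0.6 − 0.5 = 0.10.

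**Inputs that are assumptions.** The article gives no fallback rate and no outcome for fallback episodes. Let f be the share of post-activation episodes with fallback to paper and q the proportion of those re-observed within 3 h. The proportion within 3 h stands in for the time-to-event outcome.

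**The plan's own figure.** The stated 79.3% power cannot be reproduced uniquely, because the numbers of wards and steps are not given. A standard stepped-wedge variance formula with 11 patients per cell, ICC 0.15 and two-sided 5% alpha (sidedness is not stated) gives 80.0–80.4% for 14 wards switching one per step, depending on the variance convention. The figure is therefore plausible, and the present point does not depend on it.

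**Step 1: effect by activation status.** (1 − f) × 0.6 + f × q − 0.5.

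**Step 2: effect with fallback episodes excluded.** 0.6 − 0.5 = 0.10, whatever f and q are.

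**Step 3: bias from exclusion.** Step 2 minus Step 1 = f × (0.6 − q).

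| f | q | Effect by activation | Effect after exclusion | Bias |
|---|---|---|---|---|
| 5% | 0.3 | 0.085 | 0.100 | +0.015 |
| 5% | 0.5 | 0.095 | 0.100 | +0.005 |
| 5% | 0.6 | 0.100 | 0.100 | 0 |
| 5% | 0.7 | 0.105 | 0.100 | −0.005 |
| 10% | 0.3 | 0.070 | 0.100 | +0.030 |
| 10% | 0.5 | 0.090 | 0.100 | +0.010 |
| 10% | 0.6 | 0.100 | 0.100 | 0 |
| 10% | 0.7 | 0.110 | 0.100 | −0.010 |
| 20% | 0.3 | 0.040 | 0.100 | +0.060 |
| 20% | 0.5 | 0.080 | 0.100 | +0.020 |
| 20% | 0.6 | 0.100 | 0.100 | 0 |
| 20% | 0.7 | 0.120 | 0.100 | −0.020 |

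**Step 4: if wholly paper episodes on activated wards were counted as paper.** This is one possible reading, not a stated rule. With equal numbers of patients before and after activation, the estimate is 0.6 − (0.5 + f × q)/(1 + f). At f = 10%:

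- q = 0.3: 0.6 − 0.53/1.1 = 0.118, against 0.070 by activation (+0.048).
- q = 0.5: 0.6 − 0.55/1.1 = 0.100, against 0.090 (+0.010).
- q = 0.6: 0.6 − 0.56/1.1 = 0.091, against 0.100 (−0.009).
- q = 0.7: 0.6 − 0.57/1.1 = 0.082, against 0.110 (−0.028).

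Under either handling the sign depends on q, and the article does not give q.

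**The case against.** The strongest reply is that chart medium is only shorthand for ward status. The collection sentences speak of wards, not patients, and under a complete one-way switch the wards using paper are those not yet activated. The analysis is also tied to the roll-out: step and ward are covariates, secondary endpoints are reported by period and ward, and the Delayed Effect section examines the effect by time since implementation. The article promises a detailed statistical analysis plan, where deviations are usually classified. The warning about lower charting rates concerns fewer observations, not a change of medium, and a patient who triggers on SEND and is not observed again stays in the analysis under the 14 h rule.

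Much of this stands, and it rules out two stronger readings that a reader might infer:

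- **That patients charted wholly on paper on an activated ward are assigned to the paper arm.** The documents do not say so. The collection sentence is at ward level, and the handling of such patients is simply not fixed.
- **That SEND must look better than its introduction really was.** The bias favours SEND only if fallback episodes are re-observed later than SEND-charted ones. It is zero when they do equally well and reverses when they do better. The documents say nothing on this.

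The reply does not dispose of the exclusion. It is an explicit eligibility criterion, not a detail deferred to an analysis plan, and it applies to a post-activation admission charted on both media. That SEND is not withdrawn from a ward does not mean every later set is recorded electronically.

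A simple reversal of the exclusion would also create a fault. Keeping every episode that begins on an activated ward would readmit patients who move from a SEND ward to a paper ward, while those moving the other way stayed excluded.

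**Conclusion.** The point holds for the mixed-charting exclusion and for the absence of a rule linking exposure to activation. As written, the primary comparison is as-charted: post-activation episodes with partial SEND use are removed, and wholly paper episodes on activated wards have no stated handling. That does not match the Aim.

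The size is f × (0.6 − q). At an assumed 10% fallback this runs from +3 points (q = 0.3) through +1 (q = 0.5) and 0 (q = 0.6) to −1 (q = 0.7), against a planned effect of 10 points. Only the 0.5 and 0.6 come from the article. A bias towards SEND is plausible if fallback occurs under pressure or system failure, but it is not established. Because neither size nor direction can be known in advance, the primary analysis should not depend on them.

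**What to change.** 1. In Inclusion and exclusion criteria and in Analysis of outcome measures, define primary exposure by whether the study ward where the first eligible triggering set occurred had been activated at that time. Align the cohort wording in Sample size.
2. Do not apply the mixed-charting exclusion when the paper charting took place on a ward already activated.
3. Treat transfers between activated and non-activated wards by one rule that is the same in both directions, and give stays that cross a ward's activation date their own rule.
4. Have the existing chart assessor read the paper sheets of these post-activation episodes. Otherwise a next set written on paper could be missed and, under the 14 h rule, counted as no further observation, which would bias against SEND.
5. Keep the as-charted comparison as a sensitivity analysis, and report post-activation paper use by ward.

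The cost is protocol and analysis-plan wording plus some extra chart reading. Applying the present exclusion already requires mixed-chart episodes to be identified, but the article gives no basis for estimating how many there will be. The estimated effect may turn out smaller.
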